### Evaluation of implementation cost

The cost of novel therapies is frequently cited as the foremost barrier to implementing therapies in LMICs [28]. As part of the BHAP program, blinatumomab is donated and a partner NGO facilitates distribution. Therefore, this protocol will focus on the cost following drug delivery and will conduct a microcosting analysis related to training, supportive care management, and medication storage. Data will be collected on elements related to drug delivery as an implementation outcome, and observed AE data will be mapped against the data from expected costs from the resource-adapted best administration and management best practices. Prices for all line items will be determined from billing invoices at each hospital or using standardized assumptions. The expected administration costs and observed AE costs will be collated and reported using a previously published framework from prior costing analyses conducted in El Salvador, Ghana, and Mexico in order to ensure complete costs are accounted for [29]. As part of the annual Program Evaluation Group semi-structured interview, open-ended questions will be asked to assess the time and resource costs to determine the investments related to program initiation, delivery, and maintenance and to explore how remaining costs impact equitable distribution.

As an exploratory objective of this study, we will work with BHAP partners to document costs related to the acquisition including drug manufacturing, coordination, and shipping pending data availability as these data are relevant from a sustainability outcome perspective.

### Aim 2: To evaluate a multifaceted implementation strategy package, evaluate the training program, and evaluate how the strategy package influences implementation, clinical effectiveness, and safety of medication preparation, administration, and management

Based on a preliminary understanding of the key determinants and collaborator consensus for program development, a general program outline was designed. Discrete Expert Recommendations for Implementing Change (ERIC) strategies [30] were retrospectively identified, linked to specific CFIR domains [21], and assembled into a multifaceted 5-phase approach which describes the processes utilized to facilitate blinatumomab implementation in LMICs (Table 5). As an implementation effort focused heavily on formative evaluation, we have identified several strategies that target the organizational level used throughout this program [31]. A series of qualitative and quantitative evaluations will be used to assess the different components of the strategy plan to understand stakeholder perception of this approach and determine the effectiveness of the training program and clinical effectiveness.

**Table 5 Tab5:** Multifaceted strategy by program phase. Compilation of discrete ERIC strategies retrospectively mapped to each phase in the INOVATING program

Pre-implementation		Active implementation		Post-implementation
Phase 1: Establishing partnerships	Phase 2: Collecting baseline data and planning	Phase 3: Implementing evidence-based strategies	Phase 4: Supporting and monitoring implementation	Phase 5: Sustainability and maintenance
1. Obtain formal commitments 2 .Develop resource sharing agreements 3. Use advisory boards and workgroups 4. Work with educational institution 5. Develop academic partnerships 6. Access new funding 7. Conduct local consensus discussion 8. Identify and prepare champions	1. Conduct local needs assessment 2. Assess for readiness and identify barriers and facilitators 3. Organize clinician implementation teams	1. Develop educational materials 2. Conduct educational meetings 3. Distribute educational materials 4. Provide local technical assistance 5. Provide ongoing consultation 6. Develop and implement tools for quality monitoring 7. Remind clinicians	1. Facilitation 2. Use an implementation adviser 3. Purposely re-examine the implementation 4. Promote adaptability 5. Promote network weaving 6. Tailor strategies 7. Capture and share local knowledge 8. Audit and provide feedback 9. Obtain and use patient/consumers and family feedback	1. Develop a formal implementation blueprint 2. Make training dynamic 3. Use train the trainer 4. Stage implementation scale up 5. Use data experts 6. Visit other sites

*ERIC* Expert Recommendation for Implementing Change

### Training program evaluation

The resource-adapted training program will be evaluated in three ways. First, a knowledge assessment survey will be administered to all pediatric oncology providers who participated in the BHAP training program at LMIC sites. For pilot sites, this will be administered as part of a nested post-training assessment. Future sites will receive a baseline survey prior to training and will be repeated at 3, 6, and 12 months post-training to determine the role-specific knowledge related to the preparation, administration, and management of patients receiving blinatumomab. Second, the implementation team will complete an online Training Material Feedback Survey, designed by St. Jude, and participate in semi-structured interview #1 with the site-specific implementation team. The team will ask open-ended questions on the utility of the training program and workflow tools, experience with real-world administration, and additional training needs. Third, a standardized documentation tool was designed a priori by the multidisciplinary providers at St. Jude to record infusion interruptions and will be tested in pilot sites and adapted based on this cohort. It will be completed by the treating physicians and bedside nurses and returned for analysis. This will be an additional way to assess the effectiveness of training, hypothesizing that if training provides sufficient resource-adapted information, prolonged interruptions related to infusion issues will be minimized by standardization.

Comparisons between pre- and post-training knowledge assessment surveys will be made to assess the adequacy of training materials in providing adequate and retained knowledge of drug administration. Comparisons will also be made with assessments done over time (at 3, 6, and 12 months post-training). McNemar’s test will be used to assess the change from pre- vs post-training.

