### Aim 1: To conduct a formal assessment to characterize determinants that influence blinatumomab implementation in LMICs

For aim 1, this study will use mixed methods to evaluate the hypothesis that barriers related to inner setting and intervention characteristics impact the implementation of blinatumomab in LMICs. This will include the assessment of (1) capacity, (2) key barriers (readiness, climate, intervention complexity, cost), and (3) perceptions of leading indicator implementation outcomes (feasibility, acceptability, and appropriateness) from multiple stakeholders. For the three pilot sites, implementation assessments will occur 1 year after the training; however, for future sites, these will be part of the upfront baseline assessment. Assessments will be repeated at 3, 6, and 12 months post-training to characterize changes in perceived barriers and implementation outcomes over time (Table 4).

**Table 4 Tab4:** Assessment administration time points, target respondents, and frequency. Measurement tools including the type of data, key respondents, frequency, and time points of administration

Survey topic	Method	Respondent(s)	Frequency	Time point(s)
**Hospital assessment questionnaire**	QUAN	LMIC site physician champion	1 time	Prior to BHAP enrollment
**Complexity assessment**	QUAN	Implementation team	4 times	Pre-training, 3 and 6 months, and 1-year post-training
**Implementation Climate Scale (ICS)**	QUAN			
**Organization Readiness for Implementing Change (ORIC)**	QUAN			
**Acceptability of intervention (AIM)**	QUAN			
**Intervention Appropriateness Measures (IAM)**	QUAN			
**Feasibility of Intervention (FIM)**	QUAN			
**Knowledge assessment: nurses**	QUAN	All nurses	4 times	Pre-training, 3 and 6 months, and 1 year post-training
**Knowledge assessment: pharmacy**	QUAN	All pharmacists		
**Knowledge assessment: physician**	QUAN	All physicians		
**Training material feedback survey**	QUAL	Implementation team	1 time	3 months post-training (after the 1st patient received blinatumomab)
**Semi-structured group interviews:** **1) Training program feedback and site-specific barriers** **2) Site-specific fidelity vs adaptation**	QUAL	Implementation team	2 times	3 months post-training (after the 1st patient received blinatumomab) and 12 months post-training
**Implementation strategy feedback**	QUAN	Key stakeholders (implementation team, industry, St. Jude)	1 time	Annual review
**Program evaluation group interview**	QUAL			
			1 time	Annual review

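### The only test named for knowledge change is McNemar's, on a survey scheduled four times; pilot sites have no baseline for it, and knowledge loss in the first 3 months cannot be seen

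*Protocol article*

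**What the plan says.** Under Training program evaluation, the protocol article gives the purpose of the knowledge comparison as follows: "to assess the adequacy of training materials in providing adequate and retained knowledge of drug administration". It assigns one named method: McNemar's "test will be used to assess the change from pre- vs post-training". The sentence before that adds a further analysis without naming a method: "Comparisons will also be made with assessments done over time (at 3, 6, and 12 months post-training").

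The survey is meant "to determine the role-specific knowledge related to the preparation, administration, and management of patients receiving blinatumomab". Table 4 lists separate assessments for nurses, pharmacists and physicians, each given 4 times, on the same schedule as the other repeated surveys: "Pre-training, 3 and 6 months, and 1-year post-training".

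The two kinds of site are treated differently in the text. On future sites: "Future sites will receive a baseline survey prior to training and will be repeated at 3, 6, and 12 months post-training". On pilot sites: "For pilot sites, this will be administered as part of a nested post-training assessment". Table 4 lists the pre-training assessment without that exception.

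No yes/no outcome, pass mark or scoring rule is stated. The article does not say which of the three later surveys is the post-training one, and no survey at the end of training is listed.

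**The concern.** The named test and the schedule do not fit each other or the stated purpose well.

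- **Test.** McNemar's test takes one binary result per person (or per item) on two occasions. A survey covering several topics has to be collapsed to pass/fail, or split into many separate item tests with no overall answer. A person missing either of the two surveys contributes nothing to that comparison.
- **Pilot sites.** A pre/post test needs a pre-training value, and the pilot sites do not have one.
- **Retention.** The first survey after training comes at 3 months. Sites may apply for the drug once both sessions have been attended, and the 3-month interview is timed after the first patient. A 3-month result can therefore mix what was learned, what was forgotten and what was picked up at the bedside.

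The results are meant to guide changes to the training and to feed the Implementation Roadmap. Training that never conveyed the material and training whose effect faded call for different remedies.

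**Working it through.** The article gives no effect size, power or sample size for this comparison, so there is no figure of its own to reproduce. The head count does add up: 25 physicians + 36 nurses + 17 pharmacists = 78.

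**1. Occasions used.** Four surveys are scheduled at future sites. One McNemar test uses two of them. At pilot sites there is no pre-training survey, so there are 0 pre/post pairs among the 78 trained staff, whichever test is chosen.

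**2. Smallest result that can be significant.** With m people changing, all in the same direction, the exact two-sided p-value is 2 × 0.5^m. For m = 5 this is 0.0625; for m = 6 it is 0.031. At least six people must change before the test can reach 5%.

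**3. Power, if the survey yields a score that is cut.** Assumptions: normally distributed scores, within-person correlation ρ = 0.5, gain of d SD, pass mark at the pre-training median, two-sided 5%. The group sizes are the pilot role groups and their total. They serve only to show scale, since future-site numbers are not given.

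- Exact McNemar: p01 = P(fail before, pass after) and p10 = P(pass before, fail after). Power is the sum over m of Binomial(m; n, p01 + p10) × P(reject | m changers), where each changer improves with probability p01/(p01 + p10).
- For d = 0.4: p01 = 0.251 and p10 = 0.096. Check: the difference 0.155 equals 0.5 − Φ(−0.4) = 0.5 − 0.345.
- For d = 0.8: p01 = 0.335 and p10 = 0.047. Check: the difference 0.288 equals 0.5 − Φ(−0.8) = 0.5 − 0.212.
- Paired t-test: noncentrality = d√n / √(2(1 − ρ)), which is d√n at ρ = 0.5. For n = 36 this is 2.4 (d = 0.4) or 4.8 (d = 0.8).

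| n | Gain (SD) | McNemar | Paired score |
|---|---|---|---|
| 17 | 0.4 | 7.5% | 34.1% |
| 17 | 0.8 | 32.0% | 87.2% |
| 25 | 0.4 | 15.5% | 48.4% |
| 25 | 0.8 | 57.7% | 97.0% |
| 36 | 0.4 | 25.5% | 64.6% |
| 36 | 0.8 | 79.4% | 99.7% |
| 78 | 0.4 | 58.2% | 93.7% |
| 78 | 0.8 | 99.2% | 100.0% |

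Other settings, by simulation with n = 36 and a 0.5 SD gain:

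- Pass mark midway between the means: 40% against 83% at ρ = 0.5, and 36% against 69% at ρ = 0.3.
- Pass mark 1 SD above the pre-training mean, ρ = 0.5: 29% against 83%.

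**4. What the schedule identifies.** Suppose 40% correct before training and 70% at 3 months (assumed). The surveys would look the same under each of these end-of-training levels:

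| End of training | Initial gain | Loss, months 0–3 |
|---|---|---|
| 70% | 30 points | 0 points |
| 80% | 40 points | 10 points |
| 95% | 55 points | 25 points |

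The observed change from baseline to 3 months is 30 points in all three. By contrast, change from 3 to 6 to 12 months, and the level at 12 months against baseline, are direct contrasts of surveys that future sites will have.

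**The case against.** Four points can be made for the plan.

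- **McNemar may be used item by item.** The article never calls the result a score. Items marked correct or incorrect are binary, and McNemar's test is valid for them. This stands: the test is not wrong, and the power table applies only if a score is cut. It remains true that separate item tests give no overall estimate.
- **The time course is not ignored.** A reader might infer that the plan reduces everything to one pair. It does not: comparisons at 3, 6 and 12 months are also planned. Leaving their method, the handling of missing surveys and site clustering to the full protocol or SAP is normal for an article, and is no fault in itself.
- **Retention is not out of reach.** A reader might infer that retained knowledge cannot be measured at all. The article does not define retention against an end-of-training level, and two useful forms of it are estimable at future sites. Only the first 3 months are unidentified.
- **The power loss is not uniformly large.** A reader might take it that most of the power is thrown away. That holds for modest gains in small groups. With 78 people and a 0.8 SD gain the difference is negligible (99.2% against 100.0%). The article makes no power claim here, and the work is largely formative.

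These points narrow the concern. They do not supply a baseline for the pilot sites, nor make a two-occasion binary test the better choice for a survey taken four times.

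**Conclusion.** The concern holds in a limited form. McNemar's test is usable but imprecise for this survey, and neither the binary outcome nor the post-training visit is fixed. If a score is cut, the cost for 36 staff runs from about 26% against 65% power (0.4 SD gain) to about 80% against 100% (0.8 SD), and it is heavier in smaller groups. These figures rest on assumed gains, correlation and pass mark, and on group sizes borrowed from the pilot sites.

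Two points need no assumptions. No pre/post test can be run on the 78 pilot staff, which Table 4 does not acknowledge. And knowledge lost between the end of training and month 3 cannot be told apart from knowledge never gained. A better analysis is available at little cost, so the change is worth making.

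**What to change.** - **Main analysis, future sites.** Analyse percent correct with a linear mixed model: time as categorical, site as a fixed effect, a random intercept for provider, all available surveys included. Fit it separately by role or with a role-by-time interaction, because the three role instruments differ and should not be pooled into one common gain. Report changes from baseline and from 3 months with 95% confidence intervals.
- **Item level.** Keep paired percentages by item, with McNemar's test if wanted, as description.
- **Pilot sites.** State in Table 4 that they have no pre-training survey, and describe their post-training results only.
- **Retention.** Limit the claim to persistence from 3 to 12 months and to 12 months against baseline.
- **Optional.** At future sites, give the same short online survey on completion of training. Tie it to completion by either route, since Table 3 also admits staff who watch the recording. The claim could then cover the first 3 months as well.

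The cost is slightly more analysis work, a note in Table 4 and, if the option is taken, one more short survey.

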### Strategy assessment

Previous work has characterized the utility of different implementation strategies in HICs [32]; however, we do not know how different collaborator groups involved in LMIC implementation efforts will resemble those conclusions. Collaborator engagement is particularly important for the real-world application of oncology treatments, and sustainability of the drug donation program relies on input, coordination, and alignment from multiple stakeholders. Therefore, a quantitative implementation strategy feedback survey (Table 4) will be administered to assess the feasibility and importance of different implementation strategies utilized in each phase of the program to representatives from each respective stakeholder group (St. Jude, Amgen, and local implementation team) 12 months after training. After completing the survey, the research team will compare and contrast the findings between different stakeholder groups. At the annual Program Evaluation Group interview, the research team will then ask open-ended questions about experience with the different strategies to stakeholders from the three groups. During these meetings, researchers will take field notes and use thematic analysis to interpret the results. The focus of the thematic coding process is process improvement.

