### Phase 3: Training program design and delivery

In order to prioritize patient safety and to build knowledge base and skills for the medical team to recognize and respond to AEs, we selected a training program as our primary strategy. The BHAP core team created learning objectives informed by LMIC preliminary capacity assessments and site-specific multidisciplinary training needs to tailor the program to the supportive care capacity of sites. These objectives guided the content creation for a comprehensive, context-adapted training program, including didactic presentations, treatment templates, administration and management guidelines, role-specific workflow materials, and caregiver handouts. Materials were developed by the St. Jude multidisciplinary team, and the content was reviewed by the BHAP core team. Given the COVID-19 pandemic restrictions, we transitioned to an online program, with virtual synchronous sessions and recordings posted to an online classroom on the Cure4Kids platform (http://www.cure4kids.org) along with workflow materials. For pilot sites, all training materials and surveys were administered in English; however, translation and validation will be performed based on the needs of future sites. Training was delivered to 78 healthcare providers (25 physicians, 36 nurses, and 17 pharmacists) and sessions conducted independently for each pilot site as two 90-min live, interactive virtual sessions. The content for the first session focused on general information related to blinatumomab indications, mechanism of action, efficacy, and AE profile and was delivered to the combined multidisciplinary team. The second session were provider-specific, with content focused on the management issues related to roles. These didactic sessions were facilitated by a St. Jude pediatric oncologist, a nurse, and a pharmacist, with time for group discussion. The training meetings highlighted the importance of prompt response when managing patients on immunotherapy and modeled risk-reducing communication techniques between providers. After the multidisciplinary team attended the two training sessions, centers could apply for blinatumomab on a per-patient basis, at which point the medication would be shipped and sites could begin administration.

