### Methods

This convergent, mixed methods study addresses stated research questions based on the CFIR framework. Table 2 lists data sources. Qualitative methods include open-ended questions, stakeholder interviews, and meeting notes. Quantitative methods include surveys and secondary clinical and costing data. Methods will define the barriers and facilitators and explore the impact of these barriers and strategies on implementation outcomes, including feasibility, acceptability, appropriateness, and clinical effectiveness of blinatumomab in resource-limited settings using an effectiveness-implementation hybrid type 2 case series design. Due to ethical implications and prioritization of patient safety in these centers, randomization is not possible.

**Table 2 Tab2:** Study data sources including data collector, data collection method, correlation to specific CFIR domain, and target study participant. Matrix of data collection methods

Type of data	Data collectors	Data collection method	CFIR domain	Study participants
Primary data	BHAP core team	Hospital assessment questionnaire	Inner setting	Pilot center physician champion
	St. Jude research team	Provider knowledge assessment	Inner setting	Multidisciplinary pilot center providers
		Organization Readiness for Implementing Change (ORIC)	Intervention characteristics	Pilot center implementation team
		Implementation Climate Scale (ICS)	Inner setting	Pilot center implementation team
		Complexity of intervention assessment	Intervention characteristics	Pilot center implementation team
		Implementation outcome surveys (Feasibility of Intervention Measure, Acceptability of Intervention Measure, Intervention Appropriateness Measure)	Intervention characteristics	Pilot center implementation team
		Strategy ranking survey	Process	Pilot center implementation team
		Stakeholder interviews (barrier assessment, informed adaptation of patient eligibility criteria and training materials, strategy prioritization, and assessment)	Inner setting Process Intervention characteristics Outer setting	Key stakeholders
		Meeting notes	Process	Key stakeholders
		Group interview (strategy analysis, feedback on training strategy, implementation outcome, team dynamics, identifying unanticipated challenges, and adaptation of implementation, provider satisfaction)	Inner setting Process Intervention characteristics	Pilot center implementation team

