*LMICs* Low- and middle-income countries, *BHAP* Blincyto® Humanitarian Access Program, *QUAN* Quantitative, *QUAL* Qualitative

We selected well-established measurement tools that have been validated in HICs and were chosen because they are pragmatic, reviewed and agreed upon by stakeholders, and when compiled have less than 50 questions that can be completed in less than 30 min. The quantitative surveys to assess barriers include the Implementation Climate Scale (ICS) [24], Organizational Readiness for Implementing Change (ORIC) [25], and a complexity assessment. Implementation outcome survey assessments include Acceptability of Intervention Measure (AIM), Intervention Appropriateness Measure (IAM), and Feasibility of Intervention Measure (FIM) [26]. These measures of implementation outcomes were selected for their salience with stakeholders and because they are considered “leading indicators” of implementation success for early-stage initiatives [26]. Survey data collected online through Qualtrics will be housed at the Department of Global Pediatric Medicine at St. Jude.

The research team will conduct two semi-structured group interviews with the implementation team to collect additional insights into the site-specific determinants. Interview #1 will be done 3 months after training and after the site has started administering blinatumomab. The CFIR Interview Development Tool will guide the development of the interview guide and will be adapted based on experience with the pilot sites [27]. The team will ask open-ended questions about the implementation processes, barriers, and facilitators and will elicit feedback on the training program. Interview #2 will be done 1 year after training, wherein the research team will ask open-ended questions on site-specific fidelity vs adaptations to recommended administration guidelines, strategies, emerging determinants, costs, team dynamics, adequacy of training program, utility of standardized documentation tools, and parent perception of treatment.

Interviews will be audio-recorded and transcribed verbatim, and the team will use thematic coding methods to analyze and interpret the results. Written transcripts will be reviewed independently by two research team members to identify emergent themes to build a codebook. Then, each transcript will be reviewed again using the codebook. The thematic coding process will focus on process improvement.

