### Aim 3: Prepare an implementation roadmap reflecting important determinants of implementation success and implementation strategies to support the translation of blinatumomab into future LMICs.

In aim 3, the results from analyses for aims 1 and 2 will be compiled to fully characterize the relevant contextual barriers, key implementation strategies, implementation outcomes, and areas of adaptation vs fidelity to facilitate the successful implementation of blinatumomab (Table 6).

**Table 6 Tab6:** Data use to address specific research questions. Key research questions in the INOVATION program mapped to specific measurement tools used to address each question

Research question	Data source
*(1) Can blinatumomab be adapted for LMIC settings, and is it feasible, acceptable, and appropriate?*	1) Implementation outcomes assessments (FIM, AIM, IAM, cost) 2) Semi-structured interviews 3) Program evaluation group interview
*(2) Does an adapted multidisciplinary training program improve these implementation outcomes?*	1) Knowledge assessments 2) Implementation outcomes assessments (FIM, AIM, IAM, cost)
*(3) Are there contextual factors (readiness, capacity, perceived complexity) that correlate with successful implementation?*	1) Hospital assessment questionnaire 2) Barrier assessments: complexity assessment, ICS, ORIC 3) Implementation outcomes assessments (FIM, AIM, IAM) 4) Semi-structured interviews
*(4) What are the key strategies as perceived by stakeholder groups and are these the same between different groups?*	1) Implementation strategy feedback 2) Program evaluation group interview
*(5) What is stakeholder satisfaction with this implementation-guided approach?*	1) Semi-structured interviews with implementation teams 2) Program evaluation group interview
*(6) Is the effectiveness of this adapted administration of blinatumomab the same as what has been documented in high-income settings?*	1) Patient enrollment information 2) Patient safety record: adverse event reporting 3) Management records: interruption record 4) Clinical outcome data

*LMICs* Low- and middle-income countries, *FIM* Feasibility of Intervention Measure, *AIM* Acceptability of Intervention Measure, *IAM* Intervention Appropriateness Measure, *ICS* Implementation Climate Scale, *ORIC* Organizational Readiness for Implementing Change

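### Stakeholder satisfaction (research question 5) is mapped only to group interviews run by the program's own institution, which leaves a risk of favourable reporting that those sources cannot reveal

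*Protocol article*

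**What the plan says.** Table 6 (under Aim 3) lists the data sources for research question 5, on stakeholder satisfaction, as "1) Semi-structured interviews with implementation teams 2) Program evaluation group interview". Nothing else is mapped to it.

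The format of the first source is given under Aim 1: "The research team will conduct two semi-structured group interviews with the implementation team". Table 4 also calls these group interviews. For the second source, Table 4 names the respondents as "Key stakeholders (implementation team, industry, St. Jude", and the Strategy assessment section says that "the research team will then ask open-ended questions about experience with the different strategies to stakeholders from the three groups".

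Table 2 (Methods) gives the collector of the interview data as the "St. Jude research team". It places provider satisfaction among the topics of a group interview whose participants are the pilot center implementation team. The Pre-implementation section says that St. Jude and the manufacturer set up the donation program together. Under Phase 3, once staff had been trained, "centers could apply for blinatumomab on a per-patient basis".

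**The concern.** The people asked about their satisfaction depend on the program for a donated drug. They answer in a group, beside colleagues of other professional roles, to an interviewer from the institution that co-created the program and wrote its training materials. In the second source, two of the three respondent groups are themselves partners in running the program. Each of these features gives respondents a reason to hold back criticism, and all of them push in the favourable direction.

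What is at stake is whether a favourable finding on research question 5 can be read. The results of Aims 1 and 2 feed the Implementation Roadmap. If satisfaction is reported as high, neither mapped source can tell real satisfaction from courtesy, because both share the same setting and the same interviewer.

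**Working it through.** No arithmetic on a satisfaction rate applies. The article gives no rate, target or sample size for research question 5, and the planned analysis is thematic. The check is a cross-reading.

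**Step 1: the two mapped sources**

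| Feature | Site implementation-team interviews | Program Evaluation Group interview |
|---|---|---|
| Group format | Yes (Table 4; Aim 1 text) | Yes (Tables 4 and 6) |
| Conducted by | Research team (Aim 1); St. Jude in Table 2 | Research team (Strategy assessment) |
| Respondents | Implementation team only | Implementation team, industry, St. Jude |
| Manufacturer a respondent | No | Yes |
| Individual or unnamed answers | No | No |

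Sources that are individual or unnamed: 0 of 2. Sources with the manufacturer among the respondents: 1 of 2.

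**Step 2: is this peculiar to research question 5?** In Table 6, research questions 1 to 4 each have at least one survey or questionnaire. Research question 4 pairs the strategy feedback survey with the same Program Evaluation Group interview. Research question 5 has interviews only.

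**Step 3: does another instrument already cover satisfaction?**
- The acceptability, appropriateness and feasibility measures (AIM, IAM, FIM) concern the intervention and are mapped to research questions 1 to 3.
- The Training Material Feedback Survey concerns the training materials.
- The strategy feedback survey asks how feasible and how important each strategy is, and is mapped to research question 4.
- Participant satisfaction in Table 2 comes from patients and families through local providers.

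None of these is mapped to research question 5, and none asks the staff, industry and academic stakeholders how satisfied they are with the approach.

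**Step 4: is there a vehicle for a direct measure?** Yes. The strategy feedback survey goes to "representatives from each respective stakeholder group (St. Jude, Amgen, and local implementation team) 12 months after training".

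**Step 5: how small are the teams?** Table 3 requires at least 2 physicians, 2 nurses and 1 pharmacist per site, so the minimum is 2 + 2 + 1 = 5. Over the three pilot sites the minimum is 3 × 5 = 15 local respondents. Five people at one site give little anonymity; 15 pooled give more.

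**The case against.** The strongest reply is that the article shows a plausible risk and nothing more. That stands. Whether dissatisfaction would go unspoken, and by how much, cannot be learned from the article.

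Several further points also stand and limit what can be said:
- A reader might infer that staff must speak about satisfaction in front of the drug donor. The documents do not support this for the site interviews, which are with the implementation team alone, and Table 2 puts provider satisfaction in an interview of that kind.
- A reader might infer that the three groups sit together in the Program Evaluation Group interview. The section names the groups and refers to meetings, but states no joint sitting.
- The text says "researchers will take field notes and use thematic analysis to interpret the results". That does not exclude recording, so a contrast with the transcribed site interviews should not be pressed.
- Differences between stakeholder groups belong to research question 4, which has its own survey. Research question 5 asks for no comparison by group or staff role.
- Joining the donation program does not oblige a site to join the research, and the manufacturer takes no part in recruitment. This lessens the pressure to take part. It does not change who conducts the interviews or where the drug comes from.
- Confidentiality and facilitator arrangements may be in the full protocol, and their absence here is no finding.

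It can also be said that the acceptability measure and the training feedback survey offer an informal check on overly warm interviews. This stands only in part, since they measure other things and Table 6 does not use them for this question.

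What the reply does not remove is the mapping itself. Table 6 states outright which sources answer research question 5, and both are group interviews run by the program's institution.

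**Conclusion.** The point holds as a minor design weakness. Research question 5 rests on two group-interview sources, 0 of 2 individual or unnamed, both conducted by the research team of the institution that co-created the program. One of the two also has the manufacturer and St. Jude as respondents. Because sites rely on the program for drug, favourable reporting is a reasonable risk that these sources cannot reveal.

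The tempting stronger conclusion is that the satisfaction result will be biased upward. The documents do not support it: upward is the plausible direction, but neither the presence nor the size of a bias can be shown.

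The conclusion assumes that Table 6 is the complete mapping for this question and that the research team named in the text is the St. Jude team of Table 2.

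**What to change.** Add a few individual satisfaction items to the 12-month strategy feedback survey. Have them returned without names and tagged only by stakeholder group. If the rest of that survey is returned with names, put the items on a separate, unlinked form. List the survey as a source for research question 5 in Table 6, and keep the group interviews to explain what it shows.

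The cost is a slightly longer survey. Anonymity stays limited where a site team may have five members, so report the local-team answers pooled across sites. The article does not give the number of industry and St. Jude respondents; if these groups are small, their answers carry the same limit.
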